## Abstract

**Background:**

HIV pre-exposure prophylaxis (PrEP) is recommended for populations at high ongoing risk for infection. There are noted racial disparities in the incidence of HIV and other sexually transmitted infections (STIs) for African, Caribbean, and Canadian Black (ACB, black) populations in Ontario, Canada. Although blacks represent only 4.7% of the Ontario population, they account for 30% of HIV prevalence and 25% of new infections in the province. The existing clinical public health practice toolkit has not been sufficient to optimize PrEP uptake, despite the overwhelming evidence of PrEP’s efficacy for reducing HIV transmission risk. Since its establishment as an effective HIV prevention tool, the major focus in behavioral research on PrEP has been on understanding and improving adherence. To date, there is no known formalized intervention in place designed to support ACB men and women at high risk of making high-quality decisions regarding the adoption of PrEP as an HIV prevention practice.

**Objective:**

We propose 2 aims to address these gaps in HIV prevention and implementation science. First, the Ottawa Decision Support Framework (ODSF) for use in the PrEP decisional needs of black patients was adapted. Second, the decision support intervention to estimate effect size compared with control conditions in reducing decision conflict and predicting adherence over 60 days was pilot tested.

**Methods:**

In aim 1, we propose a cross-sectional qualitative descriptive study using data collected from key informant interviews with eligible PrEP patients (n=30) and surveys with health professionals (n=20) involved in HIV PrEP management. Data obtained from aim 1 will be used to develop a decision support intervention based on the ODSF. In aim 2, the adopted decision support intervention using a block-randomized design to estimate effect size compared with control conditions in reducing decision conflict and predicting adherence over 60 days was pilot tested. Hypothesis testing will be de-emphasized in favor of generating effect size estimates.

**Results:**

A research award was funded on March 25, 2017 (Multimedia Appendix 1). Ethical approval was received on March 25, 2019 (with supplemental approval received on May 10, 2019). Data collection started on April 9, 2019. As of September 30, 2019, we enrolled 29 patients and 24 health care providers for aim 1. We are currently analysing the data collected for aim 1. Aim 2 is scheduled to start in May 2020.

**Conclusions:**

This study will provide evidence-based information on the decisional needs of black patients who are at risk of HIV and have been offered PrEP. The study will also test the effect of decision support intervention in reducing decision conflict, adoption of PrEP, and adherence to PrEP.

**International Registered Report Identifier (IRRID):**

PRR1-10.2196/15080

## Introduction

### Background

HIV preexposure chemoprophylaxis (PrEP) is recommended for populations at high ongoing risk of HIV infection [1]. There are noted racial disparities in the incidence of HIV and other sexually transmitted infections (STIs) in African, Caribbean, and Canadian Black (ACB) populations in Ontario. Although blacks represent only 4.7% of the Ontario population, they account for 30% of the HIV prevalence and 25% of new infections in the province. There are also especially high rates of HIV in black individuals with a history of STI diagnosis [2,3]. Significant scientific gaps remain regarding the best strategies for supporting PrEP scale-up among blacks. Research evidence on self-determination theory (SDT) indicates that informed and autonomous decision making is a central component in facilitating motivation for long-term maintenance of health behaviors, such as orally taking PrEP daily. This concept has been demonstrated in clinical trials across various populations and health domains [4-9] but has only recently received attention in HIV prevention [10-12]. Considering that decisions regarding whether to start and continue using PrEP can be complex, there are no known studies that have investigated the decisional needs of black patients who are asked to consider taking PrEP. Furthermore, there is no known intervention that provides decisional support to blacks making choices concerning PrEP initiation. There is also a gap in evidence on how the quality of black patients’ decisions to initiate PrEP is related to PrEP adherence.

The existing clinical public health practice toolkit has not been sufficient to optimize PrEP uptake [13-28], despite the overwhelming evidence showing PrEP’s efficacy in reducing HIV transmission risk [29-33]. Since its establishment as an effective HIV prevention tool, the major focus in behavioral research on PrEP has been in understanding and improving adherence [34-40]. To date, there is no known formalized intervention in place designed to support ACB men and women at high risk of making high-quality decisions regarding the adoption of PrEP as an HIV prevention practice. We define *adoption* as an internally endorsed commitment to integrating PrEP into one’s personalized risk reduction plan. This is distinguished from the important concept of *adherence*, which refers to compliance with a medication administration schedule.

### Objectives

We propose 2 aims to address these gaps in HIV prevention and implementation science:

Adapting the Ottawa Decision Support Framework (ODSF) for use in the PrEP decisional needs of black patients (Multimedia Appendix 2).Pilot testing the decision support intervention using a 2-arm randomized design to estimate effect size compared with the control condition in reducing decision conflict and predicting adherence over 60 days.

## Methods

### Characteristics of the Research Population

#### Number of Subjects

We will enroll a maximum of 90 (aim 1: n=50, 30 patients, 20 service providers; aim 2: n=40) participants in the study. We expect that 1 in every 3 persons that we screen will enroll in the study; thus, we anticipate screening 140 individuals to reach our enrollment goal.

#### Age of Subjects

We will enroll subjects ≥18 years of age. We excluded children under the age of 18 years because we assessed that the risk of a confidentiality breach was heightened for the youth under the legal age of emancipation. Furthermore, the youth in this age range may require parental/guardian consent for research participation and medical procedures. Complying with such requirements may increase the risk of inadvertent disclosure of information that the youth may have wanted to remain private. With these complexities in mind, we cannot justify the risk of enrolling people aged younger than 18 years as our primary research aim can reasonably be addressed without their inclusion. We are also restricting the enrollment of individuals aged older than 65 years to minimize the potential for confounding due to aging-related neurocognitive factors.

#### Gender of Subjects

We will include both men and women (cisgender and transgender inclusive). We will monitor participant enrollment for aim 1 and aim 2 to ensure that there is an equitable gender distribution in the study. We will not apply gender enrollment targets to the recruitment of health care professionals.

#### Racial and Ethnic Origin

The sample will consist only of individuals who are racially categorized as black. The research questions addressed in this proposal are specific to blacks. The focus on blacks in Canada is due to their disproportionate representation in Canada’s HIV epidemic. Given this, black racial homogeneity is essential to the internal validity of the study, and thus, it is inappropriate to enroll nonblacks into this study. Owing to generations of immigration coming into Canada from countries in Africa and the Caribbean, the black population is ethnically and culturally heterogeneous. We, therefore, expect considerable ethnocultural diversity in the sample; however, we will not set enrollment targets based on culture or ethnicity. We will not apply race/ethnicity criteria to the recruitment of health care professionals.

### Inclusion Criteria

A subject will be eligible for study participation if they (1) are aged at least 18 years, (2) identify as an African, a Caribbean, and/or a Canadian black, (3) currently live in the Greater Toronto Area (GTA), (4) can speak and understand English, and (5) are assessed by the referring health care provider as being a good candidate for starting HIV PrEP.

A health care professional will be eligible for study participation if the following conditions are fulfilled:

Are employed at a participating clinical or community-based agency.Have a health care role involved in any component of the PrEP care continuum including the following:Identifying individuals at the highest risk for contracting HIVIncreasing HIV risk awareness among these individualsEnhancing PrEP awarenessFacilitating PrEP accessLinking to PrEP carePrescribing PrEPPrEP clinical managementSupporting PrEP adherenceRetaining individuals in PrEP care

### Subject identification, Recruitment, and Consent

#### Subject Identification

A venue-based nonprobability sample will be used to identified 12 clinical and community-based agencies. The 12 participating agencies located in downtown Toronto and suburban areas of the GTA with high concentrations of black residents include the following:

St. Michael’s Family Practice UnitSumac Creek Health CentreSt. James Town Health CentreSt. Lawrence Health CentreHealth Centre at 80 Bond StreetHealth Centre at 410 SherbourneWomen’s Health in Women’s Hands Community Health CentreAfricans in Partnership Against AIDSChurch Wellesley Health CentreTaibu Community Health CentreBlack Coalition for AIDS PreventionCommittee for Accessible AIDS Treatment

Staff employed at the participating clinical and community-based sites will identify prospective participants that meet basic study-defined eligibility criteria for HIV PrEP as described in the inclusion and exclusion criteria of this protocol. Once it is determined that a potential participant meets the eligibility criteria, the staff will inform the patient about the study’s existence and inquire if they want to be contacted by a research assistant (RA). If the person agrees to be contacted, then the staff will ask the patient (potential study participant) to provide written consent to release their information to the research team. Once written consent is obtained, the staff will relay the person’s contact information to the study office. An RA will follow up with the patient by phone to further explain the study and to conduct a confirmatory eligibility screen. Eligible participants will be invited (with assistance if necessary) to visit the study office at [name] for informed consent and enrollment.

Some participants identified through the participating clinical and community-based agencies may elect to receive the study’s contact information and call the study office, in lieu of (or in addition to) authorizing site staff to release their personal contact information to the RA. Participants who contact the study office will be given a brief overview of the study and asked if they wanted to learn more details. If the person is interested in knowing more about the study, then the RA will further explain the study and conduct an eligibility screen. Eligible participants will be invited (with assistance if necessary) to visit the study office at [name] for informed consent and enrollment.

#### Subject Recruitment

We will recruit primarily from community-based and clinical providers. Personnel at the selected participating clinical and community-based agencies will assist with recruitment. RAs will be available by phone during the same operating hours as the participating clinical and community-based agencies in order for them to (1) be reached by phone by someone attempting to make a referral and (2) initiate contact with a potential participant within the same business day. The RA’s role in the recruitment process is to screen for initial interest and, if the person is interested, to then screen the potential participant to determine if they are a match to the eligibility criteria. The RA will then initiate informed consent procedures and enrollment into the study.

#### Process of Consent

The RAs will be responsible for obtaining and ensuring informed consent from study participants. The RAs will fully explain the study and answer all questions regarding the participants will be asked to do as part of the study. RAs will receive training on informed consent so that during outreach activities, they can tell potential participants what to expect. In most cases, the RAs will perform the informed consent procedures as a contiguous process with recruitment. We will ensure that all participants know that their participation is completely voluntary and that they can withdraw at any time without repercussions. Once a participant verbally indicates to the RA that all their questions have been satisfactorily answered, we will document that the person has given informed consent to participate by having them sign an informed consent form. The paper copy will be stored in a locked filing cabinet. The informed consent does not end at this phase but continues throughout the entire time that the participant is engaged with the study. In service of this critical point, the RAs are responsible for ensuring that the participant understands what it is that they are being asked to do as part of the study throughout the time that the subject is enrolled, so that their participation always remains informed and volitional.

#### Illiterate and Visually Impaired Participants

Participants who are unable to read in English (defined here as illiterate) or who are visually impaired will have the possibility to select a witness who is literate and has no connection to the research team. The witness should be an adult who can confirm the accurate reading of the consent form to the participant and that the participant has given consent freely. The participant will still sign the informed consent document, and the witness will also sign attesting they understand what the participant is being asked to undertake in the study. Alternatively, participants will be given the option of having a second staff member, (a research staff who does not work on this particular research study or a staff member from the St Michael’s Hospital Family Health Team (SMH FHT) or community agency), witness the consent portion of the interview. Participants can choose the option they prefer.

### Aim 1: Methods and Study Procedures

#### Aim 1: Adapt Ottawa Decision Support Framework for the HIV Pre-Exposure Prophylaxis Decisional Needs of Black Patients

Under this aim, we will investigate 2 research questions: (1) what factors do black patients consider when deciding if to adopt HIV PrEP? and (2) How do SDT constructs of autonomy, competence, and relatedness influence black patients’ decision-making experiences regarding PrEP adoption?

#### Overview and Theoretical Basis of Self-Determination Theory Principles for the HIV Pre-Exposure Prophylaxis Decisional Needs of Black Canadians

SDT is a social psychological theory of motivation that contends that humans are naturally inclined toward health-protecting activities. These natural inclinations are optimized through the support of a human’s basic psychological needs for autonomy (volition and freedom), competence (perceived ability to attain a desired goal), and relatedness (connection to and caring from others). SDT also articulates how sociocultural factors can either facilitate or undermine volition. In this study, we will qualitatively investigate the ways in which autonomy, competence, and relatedness are present in (or absent from) PrEP decision-making experiences of black patients and use this to adapt the ODSF.

#### Evidence for Adaptation of the Ottawa Decision Support Framework for HIV Pre-Exposure Prophylaxis Decisional Needs of Black Patients

Decision support tools are a best evidence strategy in health care and improve the quality of decision making by (1) improving the accuracy of HIV risk assessment, (2) creating realistic outcome probabilities for each decision option, (3) resolving decisional conflict and increasing confidence when choosing among options, and (4) increasing satisfaction with the chosen decision. However, decision support tools have received little attention in HIV prevention and increased uptake of PrEP. Studies show that those at increased risk of HIV seroconversion underestimate their risk of HIV infection and thus may not appreciate the personal relevance of PrEP. For example, in 1 study of 7 public health clinics, 67% of people newly diagnosed with HIV rated their risk for infection as *low* or *no* risk. Studies on PrEP adoption intentions also found that self-assessing one’s behavior as *low risk* was associated with decreased intentions and the likelihood of using among men who have sex with men (MSM). Moreover, using a web-based decision aid is congruent with SDT as it promotes autonomy by eliminating perceived pressure for patients to make immediate decisions during their clinical appointment.

#### Design and Setting

We propose a cross-sectional qualitative descriptive study using data collected from key informant interviews with PrEP eligible patients (n=30) and surveys with health professionals (n=20) involved in HIV PrEP management. The study will take place in the GTA (population. 2.5 million). Over half (59%) of Canada’s black population is settled in the province of Ontario. Moreover, the majority (70%) of black people in Ontario live in GTA, making it the ideal location for this study. The trial procedures will be conducted at sites within the St. Michael’s Hospital (SMH) system, including the SMH Li Ka Shing Knowledge Institute.

#### Procedures

Using the Centers for Disease Control and Prevention guidance for emtricitabine/tenofovir (Truvada) for PrEP and/or the approved generic equivalent, we will identify prospective subjects through SMH FHT sites and community-based agencies. Staff will assess all black patients for PrEP eligibility and interest in initiating PrEP. We will purposively select subjects who want to start PrEP (n=10), do not want to start PrEP (n=10), and remain undecided (n=10) for one-on-one qualitative interviews. We will monitor sexual orientation to ensure MSM are represented in the sample. In the interviews, we will inquire about their (1) concerns about PrEP and barriers to PrEP initiation, (2) normative beliefs about PrEP, and (3) decision-making processes regarding PrEP use. We will also conduct surveys with SMH FHT staff and staff at community-based agencies who assess patient risks and make clinical recommendations for PrEP as well as those that may prescribe and/or support clinical PrEP management. We will use these qualitative findings to guide the adaptation of the ODSF for use in supporting the decisional needs of black patients who are considering PrEP. Patients will receive Can $30 (US $22) for completing the interviews. Providers will receive a Can $40 (US $29) gift card to Amazon on the web for filling in the survey tool as their participation will occur over the course of their work.

#### Data Collection

We will use several sources of data in this study. The data sources are explained as follows.

#### Demographic Surveys

We will administer a brief demographic survey to participants using the Snap Professional software (Snap Surveys). An RA will be present for this administration, although it is possible for the survey to be self-administered if this is what the participant chooses.

#### Semistructured Key Informant Interviews

We will use a semistructured interview guide for participants that includes items designed to address research questions 1 and 2 of aim 1. We will include items that are shown in the literature to impact decision-making quality. For example, we will address aim 1’s question 1 by including items that explore the perceived relevance of PrEP to their clinical situation, decisional conflict, and clarity regarding risk-reduction options and potential outcomes. We will address aim 1’s question 2 by exploring autonomy (eg, Were you told about the choices and effective options that were available to you when you were discussing PrEP?), competence (eg, What are some examples of how you were encouraged to ask questions during the discussion? How did you feel about the responses you received?), and relatedness (eg, Describe how your values were/were not understood during the discussion about PrEP?). The interviewers will also take brief field notes during the interview and will further develop more detailed notes within 24 hours.

#### Structured Surveys

We will administer a structured survey on *Facilitators and Barriers to Decision Support* using the Snap Professional software. An RA will be present to administer the survey, although it is possible for the survey to be self-administered if this is what the health care provider chooses.

#### Ottawa Decision Support Framework Adaptation

We will use inputs from the qualitative findings in aim 1, public health guidelines on PrEP, and the emtricitabine/tenofovir product monograph to tailor the ODSF for use in the Client-Centered Care Coordination (C4) PrEP decision support web-based app.

### Aim 2: Methods and Study Procedures

#### Aim 2: Pilot Test of the Adapted Decision-Support Intervention Using a 2-Arm Randomized Controlled Design

Hypothesis testing will be deemphasized in favor of generating effect size estimates. This aim will investigate 3 research questions. Preliminary hypotheses include the following:

H1: PrEP decision support reduces decision conflict in both low decisional conflict (LDC) and high decisional conflict (HDC) groups.H2: LDC + decision support group will be more likely to initiate PrEP than LDC control.H3: LDC PrEP initiators are more likely than HDC PrEP initiators to have serum levels consistent with adherence at 60 days.

#### Randomization

A block randomization strategy will be used to randomize patients in aim 2 into the experimental or control groups. Random blocks of 2, 4, and 6 are used.

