#### Pilot Procedures

We will use C4 decision support tool, which is an HTML-5 mobile web-based app that does not require device-specific configurations. Staff will provide participants with a web link to the decision-support app. When possible (ie, when a participant has a smartphone or other applicable device), staff will help participants preprogram the decision support app as both a bookmark and an icon on the participant’s device and the RA will give participants a brief tutorial on its use. Patients assigned to the experimental condition (High Decision Conflict + Decision Support and Low Decision Conflict + Decision Support) will be asked to use the bookmarked link to the decision-support website within the first 14 days (and thereafter as needed) during the study period. The routine care control group will be asked to use a bookmarked link to the frequently asked questions website on emtricitabine/tenofovir for PrEP. All groups will be compared on decision readiness and decision conflict at 14 days, self-reported PrEP initiation at 30 days, and PrEP adherence at 60 days postenrollment.

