###### Aim 2: Analysis Plan

To compare conditions, we will use analysis of covariance procedures. When we compare the 4 conditions, our primary interest will be the tests of participants who received the decision-support intervention versus the information-only control. We will test whether the decision quality, PrEP initiation, and PrEP adherence differ between conditions controlling for baseline decision-quality score. We did not conduct a power analysis to calculate sample size because we de-emphasized hypothesis testing in favor of generating effect size estimates to inform the development of a larger study.

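### The randomization section names no stratification by decisional conflict, although H1, H2 and the four-condition comparison rest on arm contrasts within the low- and high-conflict groups

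*Protocol article*

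**What the plan says.** The protocol article's Objectives describe aim 2 as "Pilot testing the decision support intervention using a 2-arm randomized design". Number of Subjects gives the size: "aim 2: n=40) participants in the study". The Randomization section consists of two statements: "A block randomization strategy will be used to randomize patients in aim 2 into the experimental or control groups" and "Random blocks of 2, 4, and 6 are used". Neither names a stratification factor, and no other section does.

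The comparisons are set out by conflict level as well as arm:

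- H1: "PrEP decision support reduces decision conflict in both low decisional conflict (LDC) and high decisional conflict (HDC) groups".
- H2: "LDC + decision support group will be more likely to initiate PrEP than LDC control".
- Pilot Procedures describes the experimental arm as two cells: "Patients assigned to the experimental condition (High Decision Conflict + Decision Support and Low Decision Conflict + Decision Support".
- The Aim 2 Analysis Plan says: "When we compare the 4 conditions, our primary interest will be the tests of participants who received the decision-support intervention", set against the information-only control. It adds that the comparisons control for a baseline decision-quality score, and that no power analysis was done because the aim is to estimate effect sizes.

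H3 compares LDC initiators with HDC initiators on adherence at 60 days.

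**The concern.** The analysis is laid out as conflict level by arm, four cells from 40 patients. The allocation, read as written, controls one margin of that table, the arm totals. It leaves to chance how the LDC patients, and separately the HDC patients, divide between the arms.

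Two things are at stake. The first is precision. H2 is an arm contrast inside LDC only, and H1 speaks of an effect in each conflict group. With about 10 patients per cell or fewer, an uneven split wastes information in the effect-size estimates that the pilot exists to produce. The second is the pooled contrast. The hypotheses treat conflict level as relevant to initiation and adherence, so if one arm happens to hold more LDC patients, part of an arm difference could reflect that mix.

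**Working it through.** **Inputs from the article.** N = 40 in aim 2; two arms; random blocks of 2, 4 and 6. The 1:1 ratio is not stated and is inferred from the even block sizes.

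**Assumption.** The article gives no LDC share. I took 12, 16 and 20 LDC patients of 40, arriving in random order. The article states no cell size, power or imbalance figure, so there is none to reproduce.

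**Step 1: how often the LDC patients split unevenly.** The scheme was simulated 10,000 times per scenario, first as one list and then as separate lists for LDC and HDC.

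| LDC patients | Mean LDC difference between arms, one list | Difference of 4 or more | Difference of 6 or more | Mean difference, two lists | 4 or more, two lists |
|---|---|---|---|---|---|
| 20 | 2.5 | 35.6% (12 v 8 or worse) | 11.8% (13 v 7 or worse) | 0.4 | 0% |
| 16 | 2.4 | 33.6% (10 v 6 or worse) | 10.4% (11 v 5 or worse) | 0.4 | 0% |
| 12 | 2.3 | 30.3% (8 v 4 or worse) | 8.2% (9 v 3 or worse) | 0.4 | 0% |

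A repeat with another seed agreed to within 1.2 percentage points. The counts above are even. With an odd count the difference is odd, so 4 or more means 5 or more, and its chance is lower: 21% at 19 LDC patients and 18% at 13.

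The 0% holds by construction. Every completed block is balanced, so only an unfinished last block can leave a difference, and a block of 6 leaves at most 3.

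**Step 2: what an uneven split costs.** With equal variances, the standard error of a contrast between cells of size a and b is proportional to √(1/a + 1/b). An equal split of the same patients gives √(4/(a+b)). The ratio of the two is the inflation.

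| Split | √(1/a + 1/b) | Equal split | Ratio |
|---|---|---|---|
| 8/12 | 0.456 | 0.447 | 1.02 |
| 7/13 | 0.469 | 0.447 | 1.05 |
| 6/10 | 0.516 | 0.500 | 1.03 |
| 5/11 | 0.539 | 0.500 | 1.08 |
| 4/8 | 0.612 | 0.577 | 1.06 |
| 3/9 | 0.667 | 0.577 | 1.15 |

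**Step 3: imbalance against scarcity.** Having 12 rather than 20 LDC patients, both split equally, raises the standard error by 0.577/0.447 = 1.29. That exceeds any inflation in the table, and stratification does nothing about it.

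**Step 4: the pooled contrast.** With arms of 20 and 20 and an LDC split of 12 v 8, the LDC share is 12/20 = 60% in one arm and 8/20 = 40% in the other.

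**Step 5: balance of the arm totals.** With one list the totals never differed by more than 2. With two lists the largest difference was 4 when both strata were even in size, reached in about 2% of runs. If both sizes are odd, the ceiling is 3 + 3 = 6, reached in at most 2 of 10,000 runs at the two odd splits tried (19 and 13 LDC patients).

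**The case against.** The strongest objection is that non-stratification is inferred from silence. The section is two sentences in a condensed article, and the wording in Pilot Procedures is compatible with allocation within conflict groups. A reader might infer that the trial is definitely unstratified. The article does not say so, and the full protocol may differ. What remains is that the section goes down to block sizes, yet describes an allocation that does not match the four cells the analysis uses.

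A reader might also infer that all three hypotheses are affected. They are not. H3 compares LDC with HDC initiators, which is not a contrast of randomized arms, and stratified allocation would not balance it.

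A third tempting reading is that the cells are likely to be badly unbalanced and the results confounded. The figures do not support that. The usual loss is a few per cent in the standard error. Chance imbalance does not bias the within-stratum estimates. The stated primary interest is the overall arm contrast, whose totals blocking keeps within 2 patients, and the analysis of covariance already controls for a baseline decision-quality score. That score is not defined or equated with the LDC/HDC class, so it may absorb part of an imbalance in the pooled comparison. It cannot restore precision lost to a small cell.

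Finally, this is an estimation pilot with hypothesis testing de-emphasized. That lowers the stakes, but precision of the effect-size estimates is still its main product.

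**Conclusion.** The point holds in a limited form. The allocation as described balances only the arm totals, while H1, H2 and the four-condition comparison need balance within LDC and HDC. Under the assumed 12, 16 or 20 LDC patients of 40, an arm difference of 4 or more LDC patients has a chance of about 30-36%, and of 6 or more about 8-12%. The loss is small at an even LDC/HDC split and reaches 15% in the standard error only at 3/9. Imbalance in the pooled comparison is a secondary cost. The result rests on the assumed LDC share, 1:1 allocation, equal variances, and the randomization section being complete as printed. It is worth changing because stratifying within the same blocks removes the larger imbalances at little cost. It does not invalidate the design.

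**What to change.** In the Randomization section:

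- Name the baseline decisional-conflict measure and the cutoff that define LDC and HDC, and state that the class is assigned before allocation. Measures for Aim 2 lists candidates, including the SURE test and the Decisional Conflict Scale, but identifies none as the classifier.
- Randomize 1:1 within the LDC and HDC strata, using the same random blocks of 2, 4 and 6 in each.
- In the Aim 2 Analysis Plan, include the stratum or the continuous baseline score in the arm comparison, and say whether the baseline decision-quality score is that score.

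If the full protocol already stratifies this way, one sentence saying so is enough.

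The cost is two lists instead of one, scoring one instrument at enrollment, and looser arm totals: a largest difference of 4 instead of 2 with even stratum sizes, and in rare cases more with odd ones. It looks feasible, since Payment for Participation already places an in-person baseline survey alongside registration, and the Results section gives aim 2 as not yet started.
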